
**Aim 1:** To determine whether the CATCH-IT 3 depression prevention intervention prevents or delays major depressive episodes, as well as non-affective disorder episodes, compared to HEALTH EDUCATION.

**Hypothesis 1:** Compared to youth in the HEALTH EDUCATION condition, youth assigned to CATCH-IT 3 will have a lower hazard ratio of major depressive episodes and non-affective disorder episodes over 2 years.

**Aim 2:** To determine if participants in the CATCH-IT 3 group exhibit more rapid favorable changes of depressive symptoms/and or vulnerability/protective factors compared with the HEALTH EDUCATION group.

**Hypothesis 2:** Compared to youth in the HEALTH EDUCATION condition, youth in the CATCH-IT 3 program will demonstrate a steeper slope of improved symptoms through growth curve analysis and fewer depressed days over two years.

**Aim 3:** To determine if participants in the CATCH-IT 3 program report lower perceived educational impairment, greater quality of life, greater health-related quality of life, and lower incidence of other mental disorders (anxiety, substance/alcohol use) as compared to participants in HEALTH EDUCATION. **Hypothesis 3:** Compared to youth in the HEALTH EDUCATION group, youth in the CATCH-IT 3 program will demonstrate more rapid benefits in reduced educational impairment, improved quality of life, and fewer disorders, as shown through steeper changes in slopes based on growth curve analysis over 2 years.

**Aim 4:** To determine for whom (moderators) and how (mediators) the CATCH-IT 3 program works in this population (Figure 1). **Hypothesis 4A:** CATCH-IT 3 effects will be moderated by six domains: (1) demographic/cultural factors, (2) vulnerability factors/adverse events, (3) motivation, (4) physician relationship, (5) parent/child co-morbid psychopathology, and (6) treatment. **Hypothesis 4B:** The relation between CATCH-IT 3 participation and reduction in depressive episodes will be mediated by adherence to the Internet and motivational interview fidelity as they alter vulnerability factors (e.g. motivation, cognition and social support) and responses to adverse events, which in turn impact the likelihood of episodes.

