## 4. Methods

### a . Research Design

**Summary:** In this 5-year, multi-site randomized clinical trial, we propose to test the efficacy of the CATCH-IT (Competent Adulthood Transition with Cognitive-behavioral Humanistic and Interpersonal Training) primary care/Internet based depression prevention intervention against Attention Monitoring Psychoeducation (HEALTH EDUCATION) in preventing the onset of depressive episodes in an intermediate to high risk group of adolescents aged 13-18. We plan to (a) identify high risk adolescents based on elevated scores on the PHQ-A, a screening measure of depressive symptoms; (b) randomize 400 (200 per Chicago sites and 200 for Boston sites) of these at-risk adolescents into either the CATCH-IT or the HEALTH EDUCATION group; (c) assess outcomes at 2, 6, 12, 18, and 24 months post intake on measures of depressive symptoms, depressive diagnoses, other mental disorders, and on measures of role impairment in education, quality of life, attainment of educational milestones, and family functioning; and (d) conduct **exploratory** analyses to examine the effectiveness of this intervention program, moderators of protection, and potential ethnic and cultural differences in intervention response. This study will enroll adolescents, parents, primary physicians and office nurse/medical assistants who are related to adolescent participation. Parents will be enrolled as study subjects in order that we can obtain information from them with regard to their child and, their key potential moderators of intervention effect and ratings of their experience. Physicians and office nurse/medical assistants are enrolled to evaluate the feasibility and sustainability of the intervention.

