## b. Eligibility criteria

### i. Adolescents

**Inclusion criteria:** (A) Youth ages 13 through 18 who are English speaking. (B) Youth must be experiencing elevated level of depressive symptoms on the Center for Epidemiologic Studies Depression (CES-D) scale (score  $\geq 16$ ) and have at least two core symptoms of Major Depression on the Patient Health Questionnaire, Adolescents. If the score is  $\geq 18$  and no personal experience of depression, the cases would be discussed among investigators and the decision for inclusion in the study would be taken in a case by case basis. This definition of current subdiagnostic depressive symptoms is consistent with the criteria used by Radloff. (C) Youth will be included if they have a past history of depression, anxiety, externalizing symptoms, or substance abuse. Youth presenting in partial remission from a major depressive episode at Baseline will be rescreened after 2 months utilizing the phone screen to ensure episode is fully remitted prior to randomization or access to study intervention. Those who do not fully remit after two months will be excluded.

**Exclusion criteria:** Adolescents must not have: (A) Current DSM-IV diagnosis (Kiddie Schedule of Affective Disorders) of Major Depressive Disorder of Dysthymia, current therapy for depression, or be taking antidepressants (e.g., SSRIs, TCAs, MAOIs, bupropion, nefazodone, mirtazapine, venlafaxine); (B) Current CES-D score  $>35$ ; (C) DSM-IV diagnosis of schizophrenia (current or past) or bipolar affective disorder; (D) Current serious medical illness that causes significant disability or dysfunction; (E) Significant reading impairment (a minimum sixth-grade reading level based on parental report), mental retardation, or developmental disabilities; (F) Serious imminent suicidal risk (as determined by endorsement of current suicide on CES-D or in KSADS interview) or other conditions that may require immediate psychiatric hospitalization; (G) Psychotic features or disorders, or currently be receiving psychotropic medication; or (H) Extreme, current drug/alcohol abuse (greater than or equal to 2 on the CRAFFT).

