## c. Justification for inclusion of any special or vulnerable populations

**Inclusion of Children:** The target age group for this intervention is adolescents ages 13-18. This is a high-risk age group for depression. The intervention requires the adolescent to participate in insight-oriented activities. Younger children may not have yet developed the cognitive ability to complete the exercises and adolescents older than 18 frequently may have already experienced an episode of depression. The goal of this intervention is to prevent the first episode.

**Women, Children, and Minorities:** Based on previous studies at our sites, we anticipate that about 60-70% of the adolescent participants will be female. Because of the emergence of gender differences in depression during adolescence (Hankin et al., 1998), we will test for gender effects in the present study, although in Clarke et al. (2001) there were no differences in the rate of change over time for males and females and no interactions between gender and treatment. We are not studying children younger than age 13 because the CATCHIT-2R intervention would require substantial adaptation for children's developmental needs. Moreover, the risk of depressive episodes is considerably lower for children below age 13 years. Our experience is that the ethnic ratio will reflect that found in the population in the cities in which the primary care practices are located (please see Target Enrollment Form Page). The geographic heterogeneity of the sites (i.e., Boston (Northeast), Chicago (Midwest)) should provide some degree of ethnic diversity. We assume an overall minority representation of about 15%, which is comparable to previous studies at these sites and representative of the populations in the communities served. We plan to over-sample minority participants.

d. Plans for subject selection, recruitment, and documentation of informed consent

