**i. Data analysis:** Descriptive statistics will be calculated for the variables. As appropriate, the Pearson chi-square test, Fisher's exact test, or analysis of variance will compare the CATCH-IT 3 and HEALTH EDUCATION groups for balance on baseline characteristics, including demographics and prior treatment history. While randomization should be successful, any variables significantly differing between groups will be included as a covariate in the analyses, along with those we expect to be related to depressive disorder (i.e., gender), and those we find to be empirically related. STATA, SPSS, SAS, and Mplus will be used for the analyses.

**Survival analyses:** We will test for constant hazard over time and if not significant at 0.10 will use Cox proportional hazards to compute the hazard ratio for major depressive episodes for the intervention group in comparison to the HEALTH EDUCATION group. If the test or diagnostics reveal non-proportional hazards, i.e. there is evidence of differential effect over time, i.e. 1-year vs 2-year outcomes; we will include this non-proportionality in analyses. We have used such limited "model fitting" tests without regard to the magnitude of intervention effect in previous analyses that still preserve the Type I error rate, and will follow multiple comparison procedures we have previously used to identify time intervals where significant effects are found.

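### The protocol states a first-episode goal, but Aim 1 pools first onsets with recurrences, so its hazard ratio cannot by itself support a first-episode claim

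*Protocol*

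**What the plan says.** Section 4.c of the protocol (Justification for inclusion of any special or vulnerable populations) explains why participants are aged 13 to 18. One reason for the upper limit is that "adolescents older than 18 frequently may have already experienced an episode of depression". The paragraph then closes: "The goal of this intervention is to prevent the first episode".

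Section 4.b.i (Eligibility criteria, Adolescents) excludes a current diagnosis of major depression or dysthymia but not a past one. Inclusion criterion (C) reads: "Youth will be included if they have a past history of depression, anxiety, externalizing symptoms, or substance abuse". It continues: "Youth presenting in partial remission from a major depressive episode at Baseline will be rescreened after 2 months". Those found fully remitted at that point can be randomized.

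Aim 1 (section 2) asks whether the intervention "prevents or delays major depressive episodes, as well as non-affective disorder episodes, compared to HEALTH EDUCATION". The survival analysis paragraph under Data analysis uses "Cox proportional hazards to compute the hazard ratio for major depressive episodes for the intervention group". Neither is limited to first lifetime onset. The Aim 1 power paragraph assumes 72% of controls free of depression at one year and does not divide them by history.

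**The concern.** For an adolescent who has already had a major depressive episode, an episode during the trial is an Aim 1 event but cannot be a first episode. The goal sentence in section 4.c and the Aim 1 event therefore describe different targets.

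Two things are at stake. The first is the claim. A pooled hazard ratio below 1 could arise wholly or partly from fewer recurrences, and nothing in the stated analysis would tell that apart from prevention of first onset. The second is precision. Only some of the events are first onsets, so the power stated for Aim 1 does not carry over to a first-episode claim.

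**Working it through.** **1. The stated power, for any episode**

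Inputs, all from the Aim 1 paragraph of Sample Size and Statistical Power:
- 200 per arm
- 72% of controls event-free at one year, with the same exponential rate in year 2
- hazard ratio 0.62
- attrition of 7% in each of the first four quarters and 2% in each of the next four

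Two-sided alpha of 0.05 is an assumption. The protocol gives 0.05 for Aim 4 only.

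- Control hazard per quarter: λ = −ln(0.72)/4 = 0.0821. Intervention: 0.62 × 0.0821 = 0.0509.
- Dropout hazard per quarter: μ = −ln(0.93) = 0.0726 in year 1 and −ln(0.98) = 0.0202 in year 2.
- Event probability in a quarter, among those still at risk: λ/(λ+μ) × [1 − exp(−(λ+μ))].
- Over eight quarters: 0.3901 (control) and 0.2689 (intervention).
- Expected events: 200 × (0.3901 + 0.2689) = 131.8.
- Schoenfeld power: Φ(½ × √131.8 × |ln 0.62| − 1.96) = Φ(2.744 − 1.960) = 78.4%.

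If dropout falls at the end of each quarter, the result is 135.3 events and 79.4%. Both are within two points of the stated 80%.

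**2. First-onset events only**

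The protocol does not give the share p of participants with a past major depressive episode, nor their relative hazard. Both are assumptions here. The hazard ratio is kept at 0.62.

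*Equal hazards.* First-onset events = (1 − p) × 131.8, put into the same power formula.

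*Doubled hazard with past depression.* The hazard h of those without a history is re-solved so that overall one-year control risk stays at 28%: (1 − p)·exp(−4h) + p·exp(−8h) = 0.72. For p = 50%, exp(−4h) = 0.80, since 0.5 × 0.80 + 0.5 × 0.64 = 0.72.

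| Share with past episode (assumed) | Equal hazards: first-onset events | Power | Doubled hazard: first-onset events | Recurrent events | Recurrences as share of events | Power, first onset |
|---|---|---|---|---|---|---|
| 10% | 118.6 | 74% | 111.2 | 20.1 | 15% | 71% |
| 30% | 92.3 | 63% | 76.2 | 54.6 | 42% | 55% |
| 50% | 65.9 | 49% | 48.3 | 82.5 | 63% | 38% |

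The nearest figures in the protocol are in section 3.a: 14% lifetime major depressive disorder at ages 15–17, and an estimated 20% experiencing depression by age 17. These describe adolescents generally, not this symptomatic sample, so they do not fix p.

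**3. Where history can enter the analysis as written**

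- Randomization is stratified by level of risk, which is not defined in terms of past depression (section 4.e).
- Covariates may include variables found in the data to be related to outcome (Data analysis).
- Lifetime psychopathology of parent and child is one of six moderator domains (section 3.b). The Moderator analysis paragraph plans subgroup analyses and interaction tests.

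None of these names past depression or commits to separating first onset from recurrence.

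**The case against.** The strongest reply is that the sentence in section 4.c is the outlier. It closes a paragraph about age. Aim 1, Hypothesis 1, the Cox analysis and the power paragraph all omit the word first. The Research Design summary speaks of efficacy "in preventing the onset of depressive episodes in an intermediate to high risk group of adolescents aged 13-18", and onset there need not mean first lifetime onset. Under Rationale for Selection of Subject, the paragraph on excluding youth with no symptoms or a current diagnosis states the study goal as reducing the risk of depressive episodes, and the paragraph on two-year follow-up speaks of future episodes. Admitting past depression also looks deliberate: eligibility provides for it expressly, and the longitudinal analysis section anticipates recurrence.

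This stands, and it rules out three stronger conclusions that a reader might draw:

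- *The Aim 1 hazard ratio does not answer the trial's goal.* It answers the goal that Aim 1 and the rationale section state. It falls short only of the section 4.c sentence.
- *The sample size is wrong.* The stated power is for any major depressive episode and it reproduces. The protocol claims no power for first onset.
- *The analysis ignores history.* The covariate rule and the moderator domains leave room for it.

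It is also fair to say that the first-onset powers rest on assumed shares and hazards and describe an analysis the protocol does not propose.

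The contradiction itself survives. The section 4.c sentence is current text and supports an eligibility limit, and it cannot be squared with inclusion criterion (C). Room for history through a data-driven covariate rule or a broad moderator domain is also weaker than a prespecified term for an obvious prognostic factor.

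**Conclusion.** The point holds as an internal contradiction about the target, with a consequence for what may be claimed. The primary test is valid and adequately sized for a new episode of either kind. It pools first onsets with recurrences, so a positive result would not by itself establish prevention of first episodes.

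The size of the gap cannot be fixed from the protocol. Against 78.4% for any episode, first-onset power would be about 74% at a 10% share and 49% at a 50% share, assuming equal hazards, a hazard ratio of 0.62 in both groups and two-sided alpha of 0.05. It would be lower if past depression raises the hazard. These figures illustrate the loss; they do not correct the stated power. Changing the sentence alone would be close to editorial. The substantive gain is in prespecifying history in the Aim 1 model and limiting the first-episode claim.

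**What to change.** 1. Reconcile the goal sentence in section 4.c with Aim 1, inclusion criterion (C) and the rationale section. Suggested wording: the goal is to prevent a new major depressive episode, first or recurrent. The age rationale in the same paragraph should be reworded to match; the Rationale for Selection of Subject already gives reasons for the age range that do not depend on first onset.
2. State the depressive event for Aim 1 as the first major depressive episode after randomization, whatever the history.
3. Prespecify lifetime major depressive episode from the baseline KSADS as a stratification factor or covariate in the Aim 1 Cox model, before outcomes are compared by arm. Do not leave it to the rule that admits variables found related in the data.
4. Report hazard ratios separately for participants without a past episode (first onset) and with one (recurrence), as secondary estimates. Rest any first-episode statement on the former, and say that the 80% power does not apply to it.

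The cost is a few sentences and one model term. The KSADS already records past diagnoses at baseline, and neither eligibility nor sample size changes. The downside is that first-episode prevention becomes a subgroup estimate with lower power.

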## **ii. Adolescents:**

**Recruitment of research subjects:** Participants will be identified using a public health model of screening (all adolescent patients during routine care appointments) for risk (sub-threshold depressed mood) in primary care clinics or specialty clinics (N=580, N=200 randomized from each site) encompassing diverse populations in urban, suburban, and rural areas in Chicago and Boston over 24 months. Based on our prior study, we expect that each site will need to screen approximately 5,000 adolescents in order to recruit and randomize 200 participants. We conservatively estimate that each physician will enroll 1-8 study participants, such that we plan to recruit 27-100 physicians at each site. We will recruit adolescent participants using a public health screening method at participating primary care practices. We will also have practices, if they desire, send out a template

letter to families inviting them to contact PATH directly for screening. Study team members will not have access to patient lists from the research sites.

- 1) Step 1: Screening: Adolescents will be invited to complete the screener while visiting their primary care doctor (Patient Health Questionnaire Adolescent, PHQ-A,) as a matter of routine clinical practice. They will be offered the 2 question screener by a nurse, medical assistant, or study staff while in an exam room. Screening by medical assistant or nurse was successfully implemented in our phase 2 clinical trial and has been described in prior publications. Those who screen negatively on the 2 question screener will have an option to have their contact information given to Northwestern for Project Tech (IRB#2012-0071). Potential cases will also be obtained via referrals from clinics by physicians, or through self-referral by brochures in the clinics where by parents can obtain information and call the study offices themselves directly. Flyers will be used and the flyer text posted on online forums such as Facebook or UIC websites. Participants will also be invited by a letter to contact the PATH team directly for screening if they are interested in participation. The letter will be provided by the PATH team to practices but sent and addressed by practices to avoid study staff having access to patient lists.

Step 2: Consent to be contacted by study staff with regard to study: All teens will be offered a study information brochure. The parent and adolescent will be asked if they wish to consent to have their screening form handed over to the study staff and to be contacted with regard to learning about the study and assessing eligibility. To do so, they must sign initial consent (parent)/assent (adolescent) at bottom of the form and provide contact information. The screener will then either be collected by the MA/RN or placed in a sealed envelope and returned to office or study staff present. If an envelope is used, it will state clearly "DO NOT MAIL. RETURN TO PATH STUDY. CONFIDENTIAL."

Step 3: After adolescent/parent assent/consent, primary care staff contacts the study coordinator and let them know they have signed initial consent forms. The study coordinator or a member of the research team would pick up the forms from the primary care setting.

Step 4: After obtaining initial consent from the parent and assent from the adolescent, study office conducts eligibility assessment (by phone) only to those adolescents who meet initial criteria specified on the 2 question screener. Up to five (5) call attempts are made in order to make initial contact with the participant(s). One call attempt may be replaced by a scripted email message if an email address is provided on the initial screening tool. A message is left on every other call. If no contact is made after 5 attempts, no further attempts to reach the participant are made.

Step 5: After establishment of eligibility criteria, the parent/adolescent are scheduled for enrollment/interview at their primary care office. If the teen is 18, they may attend without a parent if they desire (or if their parent is unavailable or unwilling to participate).

Step 6: Study staff meets adolescent and parent at primary care office, confirms full eligibility in face to face interview as well as consenting, enrollment and randomization of the subjects (described below). Should it be determined that a participant is in partial remission during the baseline interview, they will be rescreened by phone as described above in 2 months to determine if major depressive episode has fully remitted prior to randomization.

Step 7: Primary care physicians will be told to use usual care procedures (e.g., referrals for therapy, medication) in responding to adolescents with major depression during screening or during study participation. In addition, we will provide physicians with written materials and training so that they feel better equipped to manage adolescents who present with depressive issues.

**Informed consent procedures for Adolescents:** Potential research participants will be contacted initially by office staff in the physicians' offices. Office staff (Nurse/MA) or study staff will ask the adolescent and accompanying parent if they wish to complete an adolescent health questionnaire (2-question initial screen) that will be provided to their physician. At the bottom of the questionnaire, they will be asked if they are willing to be called by the study coordinator about the study. If they agree and are eligible based on the 2-question responses, they will be contacted by the study coordinator, who will speak with the teen and the parent about the study, conduct the phone eligibility assessment for the teen and will invite the teen and parent to meet. Those meeting inclusion criteria will be randomly assigned to the intervention or comparison group, after the meeting. At the first meeting, the study coordinator will meet with potential participants in a private office (within the physicians' office suites) and will provide a step by step review of the consent form with each participant. Parents and adolescents will have the entire study procedure explained to them, including the interviews, intervention, and questionnaires. Adolescents and parents will specifically consent to audio taping of interviews and retention of information for future studies (lack of consent to either or both of these items will not impact enrollment in the study). This is necessary to evaluate fidelity to the intervention interview guidelines. Both parent and child will complete written informed consent procedures. They will be informed that acceptance or refusal will not influence their ability to receive care from their pediatrician or other health care providers, and that they are free to withdraw at any time. Procedures for ensuring confidentiality and a statement of potential risks are included on the informed consent form. If the family chooses to enroll, they will complete the consent documents and will begin the baseline assessment. They will also be provided with copies of the consent documents to keep for their reference and retention. If a participant turns 18 during the course of the study, participants will be required to sign a new consent as a legal adult. A copy of the consent and HIPAA will be mailed to them for their review. A self-addressed and stamped envelope will be included for them to return the forms to UIC. If their birthday coincides with a scheduled in-person meeting with study staff, a hard-copy signature will be obtained.
